#### Groups

Participants allocated to the intervention group will participate in the 6-week VR experience program. Participants allocated to the control will receive the usual care provided by the LTCF, such as personal care, regular basic medical and nursing care, and social support activities, as committed by the Social Welfare Department [37].

#### Criteria for discontinuing interventions

If actual or potential harms are identified, the trial steering team will report them to the advisory panel, which will decide to consider suspending or terminating the trials.

#### Interventionists

The interventionists are trained young volunteers who are studying in a post-secondary institution (i.e., Tung Wah College). Tung Wah College requires students to attend community services for 40 h as a form of service learning, which is also a graduation requirement. Serving as a volunteer interventionist in this project will be counted as community service required by the college. The same volunteer will deliver the intervention to the same group of participants throughout the 6-week intervention period. A train-the-trainer program will be provided by the research team to the young volunteers. The program will provide standardized training to the volunteer interventionist on skills of delivering the intervention and establishing rapport with the participants (e.g., communication skills). The research officer will supervise each training session to ensure that the interventions are delivered identically across groups. The interventionists deliver the intervention in an interventionist-to-participant ratio of 1:3. To ensure good intervention fidelity, the young volunteers will be qualified to become interventionists in this program after they have completed a 2-h train-the-trainer program. The contents of the train-the-trainer cover the activities for operating the VR experience system, familiarizing with the standardized intervention implementation manual, as well as the essential communication skills with older people with physical disabilities. The research team will pay site visits to the research venue and observe the intervention by checking the implementation steps against the implementation manual. Regular research team meetings will be conducted to solve problems hindering the interventionists from following the intervention protocol.

#### Intervention fidelity

Training will be provided for the interventionists, who are young volunteers, following an intervention protocol checklist that covers the key steps of the intervention. The attendance of the interventionists to provide the intervention will be recorded by the collaborating LCTF staff members. The trial steering team will randomly visit each site weekly to monitor the implementation of the intervention by the interventionists and check if the implementation adheres to the intervention protocol checklist. Regular research team meetings will be conducted to determine whether the interventionist has followed the intervention protocol. In case of deviation from the implementation is observed, remedial training for the interventionists will be delivered until the interventionist can return-demonstrate the intervention 100% correctly.

#### Relevant concomitant care

The participants allocated to the intervention group receive the same usual care provided by the LTCF. The research team does not interfere with the usual care provided to the participants in either group. However, participants are prohibited to participate in other additional activities related to VR experiences provided by other organizations during the intervention period.

### Outcomes

Demographic data including age, gender, level of education, number of chronic illnesses, length of stay in the LTCF, and experience of participation in VR activities will be collected. Demographic data will be collected at T0 (i.e., baseline, week 0) only. The primary outcome is mental well-being. The four secondary outcomes are depressive symptoms, loneliness, health-related quality of life, and perceived social support. All outcome data will be collected at T0 (i.e., baseline, week 0) and T1 (i.e., the week immediately after the completion of the intervention, week 7).

#### Mental well-being (primary outcome)

The World Health Organization Five Well-being Index (WHO-5) will be used to measure mental well-being [43]. WHO-5 comprises five items and each item is rated by a 6-point Likert scale from 0 (at no time) to 5 (all of the time). The total score ranges from 0 to 25. A higher score indicates better mental well-being. The Cantonese version of WHO-5 showed good internal consistency (*α* = 0.86) and good concurrent validity with quality of life (*r*= 0.41–0.51) [43].

#### Depressive symptoms

The 9-item Patient Health Questionnaire (PHQ-9) will be used to measure depressive symptoms over the past 2 weeks [44]. PHQ-9 comprises nine items and each item is rated by a 4-point Likert scale from 0 (not at all) to 3 (nearly every day). The total score ranges from 0 to 27. A higher score indicates greater severity of depressive symptoms. The Cantonese version of PHQ-9 showed good internal consistency (*α* = 0.82), test–retest reliability (*r* = 0.76), and satisfactory concurrent validity with the mental component of quality of life (*r*=  − 0.60) [44].

#### Loneliness

The Chinese version of the 6-item De Jong Gierveld Loneliness Scale (DJGLS) will be used to measure loneliness [45]. The scale comprises three items measuring emotional loneliness and the other three items on social loneliness. Each item is rated on a 3-point scale (0 = no, 1 = more or less, 1 = yes). The total score ranges from 0 to 6. A higher score indicates a greater level of loneliness. DJGLS is reliable with good internal consistency (Cronbach’s = 0.76) and excellent inter-rater reliability (ICC = 0.98–1.00) and valid with good correlation with the answers to the direct question of loneliness (*r*= 0.71) [45].

#### Health-related quality of life

The Hong Kong version of the EuroQol 5-dimensions instrument with a five-level scale (EQ-5D-5L) will be used to measure health-related quality of life [46]. EQ-5D-5L consists of two parts: descriptive system and visual analog scale. The descriptive system has five dimensions: mobility, self-care, usual activities, pain/discomfort, and anxiety/depression. Each dimension is rated on a five-level scale (no problem, slight problem, moderate problems, severe problems, and extreme problems). All five health states defined by EQ-eD-5L can be converted to an index score by using a utility based on the Hong Kong value set. The utility value ranges from − 1 to 1 (0 indicates death, < 0 indicates worse than death, and 1 indicates full health). A systematic review showed that its test–retest reliability is excellent (ICC = 0.7–1.0) and its convergent validity is good (pooled rho = 0.756 for multi-attribute utility instruments) [47].

#### Perceived social support

The Chinese version of the Multiple Scale of Perceived Social Support (MSPSS) will be used to measure perceived social support [48]. MSPSS comprises 12 items from three subscales: family, friends, and significant others. Each item is rated on a 7-point Likert scale ranging from 1 (very strongly disagree) to 7 (very strongly agree). A total score is the summation of the results of all items. The possible score ranges from 12 to 84, with a higher score indicating a higher level of perceived social support. MSPSS has good internal consistency (Cronbach’s *α* = 0.92), good test–retest reliability (ICC = 0.65), and good convergent validity (*r*≥ 0.80) [48].

### Participant timeline

As shown in Table 2 and Fig. 1, potential participants will be recruited in the phase of enrolment, in which the eligibility screen and informed consent will be implemented. Then, in the phase of pre-treatment assessment (i.e., T0, baseline, week 0), demographic and outcome data will be collected. Subsequently, in the phase of allocation, participants will be randomly allocated to either the intervention group or the control group. Then, interventions will be implemented. In the phase of post-treatment assessment (i.e., T1, the week immediately after the completion of the intervention, week 7), outcome data will be collected once again.

**Table 2 Tab2:** Schedule of enrolment, intervention, and assessments (SPIRIT figure)

Timepoint	Enrolment	Pre-treatment assessment	Allocation	Intervention	Post-treatment assessment
		T0			T1
		Week 0			Week 7
Enrolment					
Eligibility screen	x				
Informed consent	x				
Group allocation			x		
Interventions					
Therapeutic VR experience				x	
Control				x	
Data collection					
Demographic		x			
Outcome					
Mental well-being		x			x
Depressive symptoms		x			x
Loneliness		x			x
Health-related QoL		x			x
Perceived social support		x			x

**Fig. 1 Fig1:**
[figure not shown]
CONSORT flow diagram: T0: Baseline for pre-treatment assessment (i.e., week 0), T1: The week immediately after the intervention (i.e., week 7)

### Sample size

In the literature, there is a lack of randomized controlled trials evaluating the effect of therapeutic VR experience on mental well-being using specifically in older people with physical disabilities. A similar study evaluating the effects of feedback-based virtual reality exercise on mental health (measured by the mental component summary of the Short-Form Health Survey–36 items) in older women showed that the between-group effect size at the follow-up timepoint is moderate (i.e., *d*= 0.407) [49].

A priori power analysis using G*Power employing the statistical test of two-tailed *t*-test (means: difference between two independent means of two groups) is employed. We assume that The level of significance is set at 0.05. The effect size *d*is set at 0.407 [49]. The power is set at 0.8. The group allocation ratio is set at 1:1. It is estimated that 192 samples are needed with 96 samples in each group. Considering the attrition rate of 11.3% referring to another similar study examining the effects of a VR hands-on horticultural therapy on institutionalized older people [28], the total sample size of the proposed study is estimated to be 216.

### Recruitment

Health talks on the topic of the use of VR for promoting mental health will be delivered in the collaborating LTCF. The residents, their family caregivers, and the staff members will be invited to attend. After the talks, recruitment will immediately begin at the scene. Both electronic (e-poster, short videos) and printed (e.g., flyers) promotional materials will be produced. The materials will be sent to the collaborating LTCF before the health talks. The collaborating LTCF will be invited to share the materials with potential participants and their family members via post, email, WhatsApp, and social media (e.g., Facebook). The project team and the staff members of the collaborating LTCF will be responsible for the recruitment continuously until the potential participants are exhausted. To ensure a high recruitment rate, the eligibility criteria and research information materials will be provided and explained to staff members of the collaborating LTCF in a research briefing session hosted by the research team. This is to ensure that the participants invited by the LTCF staff members are more likely to be eligible to join this study. It is estimated that the recruitment rate will be above 50%.

### Assignment of interventions

#### Allocation

Permuted block randomization will be used to randomly select block sizes and a group ratio of 1:1 will be used [50]. Participants will be randomly allocated into groups individually following the order of the randomized group sequence. The random allocation sequence list will be generated by the web-based application Research Randomizer [51]. The list will be generated by an independent research team member, who will not participate in any other parts of the proposed study. The research team member will assign group labels to the participants based on their sequence of entries to the study referring to the random group allocation sequence list. As a result, the group allocation sequence is concealed from other research team members.

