### Study setting

This study will be conducted in the LTCF. Participants will be recruited from residential care homes for the elderly under the governance of the Social Welfare Department in Hong Kong [36]. The list of 171 residential care homes is shown in the Supplementary Document. Invitations will be extended to the residential care homes for the elderly and those who are interested will be invited to join the study. These residential care homes for the elderly provide residential care, meals, personal care, regular basic medical and nursing care, and social support for older people who suffer from poor health or physical/mental disabilities with a deficiency in activities of daily living but are mentally suitable for communal living [37].

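### One trial-wide allocation list is used across several care homes; stratifying it by home is a cheap gain in balance and in forming VR groups, not the repair of a bias

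*Protocol article*

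**What the plan says.** All references are to the protocol article.

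- **Allocation.** Permuted blocks of randomly chosen size, 1:1. "Participants will be randomly allocated into groups individually following the order of the randomized group sequence". An independent team member holds the list: "The research team member will assign group labels to the participants based on their sequence of entries to the study". No stratification factor is named.
- **Study setting.** Homes are invited and those interested join. "The list of 171 residential care homes is shown in the Supplementary Document"; the number that will take part is not given.
- **Groups.** "Participants allocated to the control will receive the usual care provided by the LTCF", within a common commitment of the Social Welfare Department. Under Relevant concomitant care, the VR arm receives the same usual care.
- **Intervention and Interventionists.** VR is given face to face in a room of the home. One volunteer keeps the same participants for six weeks at a ratio of 1:3, and 30 of the 60 minutes of each session are group discussion. Manual and training are standardised.
- **Recruitment.** It starts at a health talk in each home and then continues until potential participants are exhausted.
- **Statistical methods.** Every GEE contains group, timepoint and group × timepoint. The primary reading is unadjusted.

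**The concern.** Blocks on a single list balance the trial as a whole. They balance a home only if its residents enter one after another. If several homes recruit at once, consecutive places on the list go to different homes and the split within any one home is left to chance.

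Two things are then at stake. First, facility differences in how residents change over the seven weeks can fall unevenly on the arms and add noise. Second, VR is a group activity in one place, and the list does not control how many VR residents a home has at one time. Volunteers may have to run incomplete groups or wait for more residents, and only the VR arm would wait. T0 is week 0, T1 is week 7 and the course takes six weeks, so the slack is about one week.

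**Working it through.** **1. The plan's own figure.** The Sample size section uses a "two-tailed *t*-test (means: difference between two independent means of two groups"), two-sided 0.05, power 0.80, d = 0.407.

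- Normal approximation: n per arm = 2(1.960 + 0.842)² / 0.407² ≈ 94.8, so 95.
- Noncentral t: 96 per arm, power 0.801. The stated 192 is reproduced.
- Attrition: 192 / (1 − 0.113) = 216.5, against 216 stated.

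Nothing in this point changes these figures.

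**2. Imbalance within a home.** Simulation of one permuted-block list. Assumptions: block sizes 2, 4 and 6, N = 192, homes of equal size. The table gives the absolute difference between arms within a home.

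| Homes × residents | One home after another: mean (95th percentile) | Fully interleaved: mean (95th percentile) |
|---|---|---|
| 6 × 32 | 0.6 (2) | 4.1 (10) |
| 12 × 16 | 0.7 (2) | 3.0 (8) |
| 24 × 8 | 0.7 (2) | 2.1 (6) |

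For a home of 12, the chance of an 8:4 split or worse has two limits:

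- fully interleaved entry, Binomial(12, 0.5): 2 × (495 + 220 + 66 + 12 + 1) / 4096 = 0.388;
- twelve consecutive entries on the list: about 0.018 by simulation.

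**3. VR group size.** In the interleaved limit, the chance that a home of 12 has a VR count that is a multiple of three is (1 + 220 + 924 + 220 + 1) / 4096 = 0.333. A complete set of threes therefore fails with probability 0.667.

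**4. Error rates under the current plan.** In the simulations of step 2, with no facility term and an assumed facility share of variance ρ of 0.05 to 0.10, type I error was 0.038 to 0.054 and power 0.79 to 0.82. Monte Carlo error is about 0.5 and 0.9 points.

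**5. What an LTCF main effect does in the planned GEE.** With complete data the group × timepoint estimate is

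mean(T1 − T0) in VR minus mean(T1 − T0) in control.

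A facility level that is the same at T0 and T1 drops out of each difference. A fit on simulated complete data gave 0.5206 (SE 0.1517) both with and without the LTCF main effect. Only facility-by-time variation can matter, so ρ must be read as the facility share of variance in the change. The documents give no value for it.

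**6. Upper bound on the gain.** Power at 96 per arm ≈ Φ(0.407 × √(96/2) / √(1 − ρ) − 1.960):

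| ρ (assumed) | 0 | 0.01 | 0.02 | 0.05 | 0.10 |
|---|---|---|---|---|---|
| Power | 0.805 | 0.809 | 0.813 | 0.825 | 0.844 |

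The gain is 0.4 to 2.0 points for ρ of 0.01 to 0.05, and 3.9 points at 0.10.

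**7. The remedy, simulated under interleaved entry** (6 to 24 homes).

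- Stratified list alone: the SD of the estimate falls by about 0 to 6%. Under sequential entry it hardly changes.
- Stratified list plus facility in the model: power 0.82 to 0.85 at ρ of 0.05 to 0.10, against 0.79 to 0.81 for the current plan. At ρ = 0.02 there is no material change.
- Facility in the model with the unstratified list: power 0.76 to 0.77 with 24 homes at ρ of 0.02 to 0.05, a loss of about 3 points.

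These runs use a single score per participant. They carry over to the planned analysis only with ρ read as in step 5.

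**The case against.** Individual permuted-block randomisation without strata is valid, and the protocol contradicts nothing by using it. Any imbalance by home is chance, which the standard error already reflects. That stands, and it is why this is an improvement rather than an error.

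It also stands that recruitment begins home by home, so residents of a home may enter in runs and the blocks would then hold the difference to about 2. Continued recruitment after the talks makes some interleaving plausible, but the documents do not say how much.

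On group formation, the protocol gives a ratio of 1:3. It does not require exactly three residents before a group starts, it sets T1 at week 7 for both arms, and it does not exclude allocation in batches. Stratifying does not guarantee threes either: a home of 10 yields about 5 VR residents. What remains is that the plan leaves group formation uncontrolled and that stratified batches make it easier.

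A reader might go further in four ways, none of which the documents support:

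- **That a badly split home is the rule**, from the 0.388 above. That value is the fully interleaved limit; the sequential limit is about 0.018.
- **That facility adjustment would be worth 10 to 20 participants** (0.05 to 0.10 × 192). That assumes an analysis of T1 scores alone, whereas the planned effect is group × timepoint, from which stable facility differences cancel.
- **That 171 homes take part.** That is the invitation list.
- **That care differs strongly between homes.** Usual care follows a common commitment and VR a common manual.

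**Conclusion.** The point holds as a modest, optional improvement. One list in order of entry allows chance imbalance within homes and leaves the number of VR residents per home uncontrolled, to a degree that depends on how far entry is interleaved. It does not bias the comparison, type I error stays near 0.05, and the planned power is kept.

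The expected statistical gain is about 0 to 3 points of power, and about 4 if facility explained 10% of the variance in change. These sizes rest on assumed facility shares, block sizes, and number and size of homes, none of which the documents give. The practical gain in forming VR groups and in similar T0-to-start times needs no assumed variance share, but it too depends on the pattern of entry. Clustering of outcomes within volunteer-led groups in the VR arm is a separate matter that stratification by home does not address.

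**What to change.** 1. In Allocation, replace the single list by one permuted-block sequence with random block sizes per LTCF, held by the same independent team member.
2. Where practical, release allocations for a home in batches once T0 is complete for the residents in that batch, so that VR groups can be formed and the time from T0 to start is similar in both arms.
3. If the analysis is to reflect the stratification, add LTCF × timepoint (with its LTCF main effect) to the GEE, or use a T1 model adjusted for baseline and LTCF. Do this only together with the stratified list, because with many small homes and an unstratified list it can lose power. An LTCF main effect alone does nothing for the planned estimate with complete data.

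Cost: one list per home, a short wait for some residents, and slightly more predictable allocation in very small homes. No extra participants are needed. The Trial status section places the trial before recruitment, so the change can be made in time.

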#### Blinding

In the proposed study, only the outcome assessor will be blinded to the group labels. Participants and interventionists are not possible to be blinded in this study. The group labels will not be known to the outcome assessors and will not appear on any documents that the outcome assessors can access. The participants, family members, and staff members of the LTCF are prohibited to disclose the group labels of the participants to the outcome assessors.

### Data collection and management

Data will be collected by the project implementation team, including one research officer and one research assistant, as well as a group of trained student helpers who are blinded to the group label for data collection in the phase of post-treatment assessment. Data will be collected using a computerized online data collection application Qualtrics (www.qualtrics.com). Qualtrics can prompt the data collectors for the unfilled data field and the data collector must provide reasons for leaving the data field blanks before they can submit the data, to minimize the risk of unintentional missing data. On the day immediately after the data collection, the data collectors will conduct preliminary data analysis to do the range check to ensure that the data are complete and the data are entered correctly. When there are missing data or out-of-range data noted, the project implementation team will investigate the causes and re-conduct the data collection as immediately as possible. Qualtrics employs many safety methods to ensure the confidentiality of the data on the server (e.g., high-end firewall system, encryption) [52]. The data on Qualitrics will be saved on the password-protected cloud server at Tung Wah College for at least seven years according to the requirement of the ethics committee after each round of data collection. Only the research team members have access right to the final full dataset after the completion of the study. To promote participant retention, a completion certificate issued by Tung Wah College will be presented to participants who completed the intervention and follow-up data collection in a celebratory ceremony. For participants who discontinue the intervention or deviate from the intervention protocol, data on all five outcomes (i.e., mental well-being, depressive symptoms, loneliness, health-related quality of life, and perceived social support) will also be collected in the week after the normal completion of the intervention (i.e., week 7).

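### The one stated retention incentive depends on completing the intervention as well as follow-up, which sits badly with an analysis that needs week-7 data from everyone

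*Protocol article*

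**What the plan says.** All quotations are from the protocol article.

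- **Purpose of the incentive** (Data collection and management): "To promote participant retention, a completion certificate issued by Tung Wah College" is offered. No other retention incentive is described.
- **Who receives it** (same sentence): it "will be presented to participants who completed the intervention and follow-up data collection in a celebratory ceremony". Two conditions are joined, completing the intervention and completing follow-up.
- **Follow-up of those who stop** (the next sentence): "For participants who discontinue the intervention or deviate from the intervention protocol, data on all five outcomes" are also to be collected in week 7.
- **Control condition** (Groups): "Participants allocated to the control will receive the usual care provided by the LTCF".
- **Outcome timing** (Outcomes): "All outcome data will be collected at T0 (i.e., baseline, week 0) and T1", the latter in week 7, with no distinction between arms.
- **Setting** (Study setting): "This study will be conducted in the LTCF". Under Eligibility criteria, every participant is a resident of such a facility.
- **Blinding** (Blinding): "Participants and interventionists are not possible to be blinded in this study". Only the outcome assessors are blinded.
- **Analysis** (Statistical methods): the primary interpretation is by intention to treat without covariate adjustment, using GEE. Missing data are handled by methods such as multiple imputation.

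**The concern.** A retention incentive exists to secure outcome data. Here it is earned partly by adherence. VR participants who stop attending are among those most likely to be missing at week 7, and an intention-to-treat analysis particularly needs their outcomes. The wording takes the incentive away from them even if they attend T1. For controls, the text does not say what completing the intervention would mean.

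Participants know their allocation, so an incentive perceived as belonging to VR completers could make willingness to be assessed at week 7 differ by adherence, and possibly by arm. If those lost differ in well-being from those retained, the comparison is biased. WHO-5 is measured only at T0 and T1, so no intermediate outcome is available to inform imputation. Imputation can recover only what the observed data predict.

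**Working it through.** **1. The text, by type of participant.** The two conditions for the certificate are set against the plan to collect T1 data.

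| Participant | Week-7 data wanted? | Certificate, as worded |
|---|---|---|
| VR, completes sessions and T1 | Yes | Yes |
| VR, stops sessions, attends T1 | Yes, stated in the next sentence | No |
| Control, attends T1 | Yes (Outcomes; Table 2) | Unclear |

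The third row is unclear for two reasons. The Intervention section and Groups use the term for the VR programme and contrast it with usual care. Table 2, however, lists the control condition under its Interventions heading, so a both-arms meaning is possible. The second row holds on either reading.

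**2. The plan's own figures.** Inputs from Sample size: d = 0.407, two-sided alpha 0.05, power 0.80, 1:1 allocation, attrition 11.3%.

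- Two-sample t-test (noncentral t): n = 95.73, so 96 per arm and 192 in total, with power 0.801. This matches the article.
- Attrition: 192 / (1 − 0.113) = 216.46, against 216 stated. The rounding is of no consequence.
- 216 / 2 = 108 randomised per arm. Attrition is not split by arm.

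**3. Illustration of bias (assumed inputs).** Let q be the dropout proportion in an arm, and let δ be the amount, in SD, by which missing participants score below completers in that arm. The full-arm mean is the completer mean minus qδ. The completers-only contrast (VR minus control) is therefore shifted by

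shift = δ × (q_VR − q_control).

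Neither the arm-specific q nor δ is in the article. With δ from 0.2 to 0.5:

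| q_VR / q_control | Difference | Shift (SD) | Size relative to 0.407 |
|---|---|---|---|
| 5% / 17.6% (mean 11.3%) | −0.126 | −0.025 to −0.063 | 6.2% to 15.5% |
| 11.3% / 20% | −0.087 | −0.017 to −0.044 | 4.3% to 10.7% |
| 11.3% / 25% | −0.137 | −0.027 to −0.069 | 6.7% to 16.8% |
| 17.6% / 5% (first row reversed) | +0.126 | +0.025 to +0.063 | 6.2% to 15.5% |

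The sign matters. If controls are lost in excess and the missing are worse off, the contrast moves against VR. If VR discontinuers are lost in excess, it moves in favour of VR. The two possible mechanisms oppose each other, so no direction can be asserted. These figures ignore imputation from baseline data; with it, δ should be read as the difference that baseline does not explain.

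**4. Power.** With 108 randomised per arm, power is 0.800 at 11.3% / 11.3%, 0.798 at 5% / 17.6%, 0.779 at 11.3% / 20% and 0.765 at 11.3% / 25%. The issue is possible bias, with little loss of power unless total attrition rises.

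**The case against.** The case for leaving the text alone has real force.

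- **Discontinuers are already covered.** The sentence after the certificate rule commits to week-7 data on all five outcomes from them, and the section provides for chasing missing data. Withholding a certificate does not contradict collecting data. This stands: the two sentences pull in different directions, but they are not inconsistent.
- **Participants live on site.** Assessors can reach them easily, and a paper certificate is a weak lever. It has no bearing on death, which Statistical methods names as one cause of missing data. This stands, and it is the main reason to expect a small effect. Residents can still decline an assessment, however, and the plan itself allows for 11.3% attrition and chose this incentive to reduce it.
- **Controls may be included.** A reader might infer that controls are shut out and that dropout is therefore made to depend on arm. The document does not support that. The sentence speaks of participants in general, and Table 2 places the control condition under Interventions. No differential dropout is stated anywhere.
- **The ceremony and blinding.** A reader might also infer that the ceremony would reveal allocation to assessors. The article gives no time, place or audience for it, participants, family members and staff are barred from disclosing group labels, and a ceremony for both arms would reveal nothing. Only a precaution is justified.
- **A condensed article.** Other retention measures may sit in a fuller protocol. That is possible, but the point concerns a rule that is stated, not one that is missing.

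**Conclusion.** The point holds in a limited form. As worded, the incentive excludes VR participants who discontinue but attend T1, and it leaves the position of controls unclear, while the follow-up plan and the intention-to-treat analysis need week-7 data from all of them. That is a risk of retention differing by adherence and possibly by arm, in a trial whose participants are unblinded. It is not evidence that this will happen.

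The size and direction of any bias cannot be derived from the article. The illustrative shifts, at most about 0.07 SD in either direction, rest wholly on assumed dropout splits and assumed differences between missing and observed participants, for an analysis of completers only. The true effect is probably small. The planned sample size is unaffected. This is a low-cost improvement to the wording and timing of the incentive, and no threat to the design.

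**What to change.** Reword the sentence so that the certificate goes to every participant, in either arm, who completes the T1 assessment, regardless of the number of sessions attended. As a precaution for assessor blinding, state that any ceremony at a facility takes place only after the last T1 assessment there.

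The cost is up to about 108 further certificates if controls are not already included, a few more for VR discontinuers, a later ceremony, and a slightly weaker incentive to attend sessions. According to Trial status, recruitment had not begun when the article was written, so the change could be made before any participant was affected.
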